## Destruction

N/A

## Treatment after study end

After the study has ended no further Hibitane® will be prescribed. If the participants have additional need for help with RVVC, they will either be taken care of at the Vulvar Clinic at Danderyd Hospital and provided routine care, or referred to their ordinal open care gynecologist.

# Methods for measurement of endpoints for clinical efficacy and safety

## Methods for measurement of endpoints for clinical efficacy

### Primary endpoint (variable)

The primary endpoint of treatment efficacy is the proportion of women in each group that has negative vaginal cultures for *Candida* albicans after 1 week after active treatment. The cultures will be analyzed at the Microbiology department at Karolinska University Hospital Solna in collaboration with professor [name].

### Secondary endpoints (variables)

1. The secondary endpoint of treatment efficacy is the proportion of women in each group that has negative vaginal cultures for *Candida* albicans at 3 months’ and 6 months’ follow-ups, after end of prophylactic treatment. The cultures will be analyzed as described under 8.1.1.
2. Adverse events will continuously be registered during the study. The participants can fill out any AE in a web based digital weekly diary but also contact the research midwife when needed. AEs will be described and summarized and compared between treatment arms regarding proportion of women with AE.
3. A symptom and examination score (composite index 0-5) will be measured first at baseline/inclusion and then at 3 follow-ups; 1 week after treatment, 3 months’ follow-up after prophylactic treatment and at 6 months’ follow-up. The investigator will ask the participant for common symptoms of RVVC (typical discharge, itching, dryness of the skin/mucosa, burning and pain). Each present symptom will generate 1 point of the composite index (range 0-5). During the gynecological examination performed at inclusion and at each follow-up, typical clinical findings (redness skin/mucosa, typical discharge, dry skin/mucosa, fissures skin/mucosa, visible candida hyfae under the microscope) will be registered in the CRF. Each finding will generate 1 point of the composite index (range 0-5). The proportion of women in each treatment arm with symptom- and examination score >2 for both the will be used for statistical analyses.
4. The content of lactobacillus in vaginal wet mount will be analyzed and semi-quantified first at baseline/inclusion and then at 3 follow-ups; 1 week after treatment, 3 months’ follow-up after prophylactic treatment and at 6 months’ follow-up. Routine procedure for wet mount (vaginal secretion with NaCl) will be performed and the amount of lactobacilli will be graded in a light microscope with high magnification (40x and 100x) (Olympus CX41) as either normal quantity (more lactobacilli compared to number of epithelial cell/view field) or reduced (less or absent lactobacilli compared to number of epithelial cell/view field). Differences in proportion of women with normal/reduced quantity between study groups x time will be analyzed. The two investigators will before the study starts, analyzed a number of wet mounts together for inter-rater reliability. All wet mounts will be photo documented via a camera connected to the microscope placed at the department of obstetrics and gynecology, Danderyd Hospital. These photos will be blinded and evaluated by the two investigators together.
5. Data on events of relapses will be collected during the prophylactic and observational phases of the study. The participants will be provided with equipment to collect self-sampled vaginal cultures for *Candida albicans* at home in case of new symptoms of infection. They can also contact the research midwife who could help out with the cultures if needed. Data on relapses will be reported in the CRF.
6. Biopsies from the vaginal mucosa will be used to study possible toxic effect on the vaginal epithelial cells. The biopsies will be taken at baseline/inclusion and at the 3 months’ follow-up and analyzed by histopathology and immunohistochemistry. The biopsies are 3-4 mm, taken by biopsy forceps after local anesthetics. The purpose of the biopsies is to investigate how CHG affect the vaginal mucosa causing possible toxic reactions of the epithelium and impairment of the local immune response. The biopsies will be microscopically examined using ordinary histopathological staining as well as immunohistochemistry for inflammatory and immunological markers. Also PCR analyses for antimicrobial peptides, cytokines, kemokins, cationic intrinsically disordered antimicrobial peptides (CIDAMP) will be performed. Biopsies from participants allocated to FLZ will serve as controls.
7. The vaginal biopsies described above will also be used to study vaginal biofilm formation before and after treatment and prophylaxis with CHG and FLZ.

All laboratory test will be carried out at Karolinska Institutet core facilities.

The biopsies will be stored in the Stockholm Medical Biobank (registration number 914, sample ID Bb142563).

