## Secondary endpoint (variables)

1. The proportion of women in each group that has negative vaginal cultures for *Candida albicans* at 3 months’ follow-up after prophylactic treatment and at 6 months’ follow-up after the observational phase of the study.
2. Analysis of proportion of women with adverse events (AE) across treatment arms. The AEs will also be reported in descriptive terms and summarized for each treatment arm.
3. Proportion of women with symptom score > 2. Each symptom of typical discharge, itching, dryness of the skin/mucosa, burning and pain will generate 1 point of a composite index (range 0-5).
4. Proportion of women with examination score >2. Each finding of redness skin/mucosa, typical discharge, dry skin/mucosa, fissures skin/mucosa, visible candida hyphae in the microscope will generate 1 point of a composite index (range 0-5).
5. Proportion of women with reduced vaginal lactobacilli content in vaginal smears measured by a semi-quantitative method as normal or reduced quantity.
6. Proportion of women with relapse of *Candida albicans* infection between end of treatment and end of prophylactic treatment (1week post treatment to 3 months’ follow-up) and between 3- and 6 months’ follow-up after end of prophylactic treatment.
7. Proportion of women with possible toxic effect on the vaginal epithelium, defined as disruption and/or inflammation of the epithelial lining, analyzed from vaginal biopsies before and after treatment and prophylaxis.
8. Further analysis of mucosa inflammatory mechanism (histopathology and immunohistochemistry) and biofilm formation during and after treatment and prophylaxis, analyzed from vaginal biopsies. The methods for these *in vitro* exploratory analyses are not yet decided on.

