## Randomization

The randomization ratio between the treatment groups will be 1:1. A computer generated block randomization of 15 participants will be performed by the research midwife. Randomization to the study medications will be carried out via opening of opaque sealed envelopes in consecutive order. All women will be identified through a patient log with name and Swedish personal identification number and a study identification number, used on all CRFs (paper and electronic). The randomization will not be blinded to neither participants nor investigators due to the differences in study medications. The primary outcome variable is objective (negative vaginal culture for *Candida albicans*) with low risk of bias.

Subjects are included/randomized consecutively as they are found to be eligible for inclusion in the study. If a subject discontinues their study participation, their subject code will not be reused and the subject will not be allowed to re-enter the study again.

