## Quality Assurance and Sponsor oversight

The clinical trial will be performed at the research department at the Department of OB&GYN, Danderyd Hospital. The sponsor has the responsibility for the monitoring plan and to assure direct access to all source data for monitoring, audits and inspections.

Only 3 personnel will be involved in the study; the principal- and co-investigator together with the research coordinator. The study personnel have long experience of working together and have planned the study in close co-operation. No special training of personnel is needed.

The study coordinator role is to book the appointments for the participants, collect data from vaginal cultures and other laboratory tests, handle the CRFs and be of help during monitoring and audits. Any AEs can directly be reported to the study coordinator and further reported to the investigators and sponsor if needed.

The principal (=sponsor) and co-investigator will conduct the study visits, give the oral and written information and collect the signed consents, check the inclusion- and exclusion criteria and decide on the final inclusion of the participants.

The major risk of the study has been identified to be correlated to the study drug fluconazole which serves as the reference treatment in the trial. Fluconazole is an approved medication and caution to avoid known AEs has been taken in the inclusion- and exclusion criteria in the protocol. No serious AEs with Hibitane is expected. Any AEs can be reported directly to the study coordinator or by the use of the electronic weekly dairy.

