## Case Report Form (Forskningspersonsformulär)

A paper Case Report Form (CRF) is used for data collected at all five study visits. An electronic CRF (Entermedic) will be used to collect some data; 1) the questionnaire on medical history and reproductive health, filled out at inclusion, 2) a weekly diary where the participants can fill out compliance to the allocated treatment, symptoms of RVVC and AEs.

The investigator must ensure that data is registered and any corrections in the CRF are made as stated in the study protocol and in accordance with the instructions. The investigator must ensure that the registered data is correct, complete, and that reporting takes place according to the timelines that have been predefined and agreed. The investigator signs the completed CRF. A copy of the completed CRF will be archived at the study site.

If an examination/test is not performed and data does not exist, ND (Not done) or NK (Not known) is marked. If the question is irrelevant NA (Not applicable) is written. Corrections in the paper CRF are done by striking out the incorrect information and adding the correct information next to the incorrect information, signing, and dating the correction.

Each study visit will also be registered in the hospital’s medical records.

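### The symptom score and the hyphae item of the examination score are recorded by investigators who know the arm, and the protocol's low-bias argument covers only the culture outcome

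*Protocol*

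**What the plan says.** **Symptom score.** The secondary endpoint is fixed as follows: "Proportion of women with symptom score > 2. Each symptom of typical discharge, itching, dryness of the skin/mucosa, burning and pain will generate 1 point". Section 8.1.2, item 3, says how it is obtained: "The investigator will ask the participant for common symptoms of RVVC". On timing, the score "will be measured first at baseline/inclusion and then at 3 follow-ups; 1 week after treatment, 3 months’ follow-up after prophylactic treatment and at 6 months’" (Visits 2 to 5).

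**Examination score.** The same item lists five findings registered in the CRF at the gynecological examination: redness, typical discharge, dryness, fissures and "visible candida hyfae under the microscope". For both scores, the proportion of women per arm above 2 is what is analysed.

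**Who knows the arm.** Under Randomization: "The randomization will not be blinded to neither participants nor investigators due to the differences in study medications". Under Quality Assurance and Sponsor oversight (11.1), the principal investigator, who is also the sponsor, and the "co-investigator will conduct the study visits".

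**Defence of the open design.** Overall study design and Randomization both argue that bias is low because the primary outcome, a culture, is objective. Neither section says anything about the two scores.

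**Related data already planned.** Section 8.1.2, item 4, has all wet mounts photographed for the lactobacilli endpoint: "These photos will be blinded and evaluated by the two investigators together". Section 14.1 describes "a weekly diary where the participants can fill out compliance to the allocated treatment, symptoms of RVVC and AEs". Procedures and flow chart sends the diary link weekly in weeks 2-24 and gives the diary a role in following compliance, efficacy and adverse events and in reporting suspected relapses.

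**The concern.** A count of symptoms elicited by interview depends partly on how the question is put and how a doubtful answer is recorded. Deciding whether hyphae are visible in a wet mount also leaves room for judgement. Both are done by people who know the treatment. They also work from an expectation, because the Background presents the group's own in vitro results favouring chlorhexidine as the basis of the trial.

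The stated reason for accepting an open design is sound for a laboratory culture. It does not carry over to these scores, and no other safeguard is given for them. At stake are two of the eight secondary endpoints, both compared between arms. If recording leans differently by arm, the lean goes straight into the proportion above 2, where it cannot be told apart from a treatment effect. The false discovery rate adjustment in section 10.3 does not help. It deals with multiplicity among valid p-values, not with a biased comparison.

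**Working it through.** **1. The plan's own figure.** The only sample size given is for the primary endpoint: 86% in both arms, margin 30 percentage points, power 90%. With one-sided 5%, n per arm = 2 × 0.86 × 0.14 × (1.645 + 1.282)² / 0.30² = 22.9, so 23 per arm and 46 in total, as stated. It does not bear on this point. No rate or size is given for either score.

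**2. Safeguards side by side.**

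| Outcome | Who records it | Stated protection |
|---|---|---|
| Culture (primary; 3 and 6 months) | Microbiology laboratory | Objectivity argument |
| Relapse between visits | Diary report, home self-sampled culture | Culture |
| Lactobacilli | Microscope grading, plus photos | Blinded photo evaluation |
| Symptom score | Investigator interview | None stated |
| Examination score, hyphae item | Investigator at the visit | None stated; not linked to the photos |

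The flow chart schedules wet-mount microscopy and the examination score at the same visits, 2 to 5. The protocol names no other microscopic preparation, so I assume that hyphae are looked for in the same mount.

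**3. How item-level leaning reaches the cut-off (assumed values).** Take five independent items, each recorded with probability p. Then P(score > 2) = 10p³(1−p)² + 5p⁴(1−p) + p⁵.
- p = 0.40: 0.230 + 0.077 + 0.010 = 0.317
- p = 0.35: 0.181 + 0.049 + 0.005 = 0.235
- p = 0.30: 0.132 + 0.028 + 0.002 = 0.163

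Under-recording of 5 points per item in one arm only would thus shift that arm's proportion by about 8 points, and 10 points per item by about 15. Equal under-recording in both arms would create no spurious difference. Real symptoms are probably correlated, so these figures show the mechanism and are not estimates.

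**4. Effect on a between-arm test (assumed values).** Setting: 30 per arm, no true difference, one arm under-scored. Test: z = (x₁−x₂)/30 ÷ √(p̄(1−p̄)·2/30), where x₁ and x₂ are the numbers above 2 and p̄ is the pooled proportion. It is two-sided at 5%, with exact enumeration of all outcomes.

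| True proportion > 2 | No bias | 5 points | 10 points | 15 points |
|---|---|---|---|---|
| 20% | 4.9% | 7.9% | 19.4% | 45.3% |
| 30% | 4.9% | 7.0% | 14.2% | 28.1% |
| 40% | 4.9% | 6.6% | 12.3% | 23.0% |

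Ten points is 0.10 × 30 = 3 women.

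**5. Share of the hyphae item.** It changes a woman's classification only if her other four findings total exactly 2. With four independent items at 40%, that probability is 6 × 0.40² × 0.60² = 0.346. A 10-point lean on hyphae alone would then move the examination proportion by 0.10 × 0.346 = 3.5 points. Blinding this item helps but protects only part of the score.

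**The case against.** The strongest reply is that self-recording does not remove the bias. Participants also know their arm, and symptoms are subjective whoever writes them down. This stands. Self-recording removes the investigator's influence, not the woman's expectation. The examination score keeps four items graded live, and sparse hyphae may not show in a photographed field, so some sensitivity may be lost.

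Three stronger readings are tempting, and the documents do not support them:
- A reader might infer that the blinded photos and the diary go unused. The photos are evaluated for lactobacilli, and the diary has efficacy and relapse-reporting roles. What is true is narrower: the symptom score's definition does not draw on the diary, and the hyphae item is not tied to the photos.
- A reader might infer that the trial misses episodes between visits. Relapse in both intervals is its own secondary endpoint, supported by diary reports and home cultures. The visit score addresses symptom status at set times.
- A reader might infer that a diary endpoint should replace the visit score because there are more readings (24 − 2 + 1 = 23 weekly links against three follow-up visits). The documents do not show that the diary records the same five items, entries may be missed, and the share of weeks with symptoms is a different variable. A power gain carried from one to the other is not supported.

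**Conclusion.** The point holds in a limited form. The symptom score and the hyphae item are recorded by investigators who know the arm, and the protocol's only argument for low bias does not cover them. The primary endpoint, the later cultures and the culture-based relapse endpoint are not touched.

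The documents give neither the rate of score above 2 nor any measure of leaning, so neither the size nor the direction of bias can be derived. The illustration rests on an assumed true proportion of 20-40% and a lean confined to one arm. On those terms, 5 points hardly matters (6.6-7.9% false positives), while 10 points does (12.3-19.4%). With 30 women per arm, a lean affecting three women is enough to make a comparison of these two endpoints unreliable. Since most of the remedy uses procedures already planned, the change is worth making before data are seen.

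**What to change.** In section 8.1.2, item 3, with a matching line in 10.2.1:

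1. At Visits 2-5, have the woman record the five symptom items herself before the investigator interviews her. Use that record for the proportion with score above 2. Including Visit 2 keeps baseline and follow-up on one instrument.
2. Score the hyphae item in the blinded photo evaluation already planned under item 4, and keep the visit reading as a sensitivity analysis.
3. Add a supportive comparison, not a replacement, of the RVVC symptoms entered in the weekly diary, separately for the prophylactic and the observational phase.
4. State that the objectivity argument applies to the culture outcomes, and that the symptom self-record and the other four examination items remain open-label.

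**Cost.** One short form at each of four visits, at most 4 × 60 = 240 forms, which can sit with the paper CRF. One more item is read from photos that the two investigators already evaluate. No new visit or reader is needed. Missing diary weeks will need a handling rule, and some sparse hyphae may be missed on photos.

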Our research group has previously done an *in vitro* study in which we analyzed the effect of FLZ and the antiseptic substance chlorhexidine gluconate’s (CHG) ability to kill fungal cells and to break down existing biofilm or prevent new biofilm formation [9]. The biofilm formation is an important stage for the fungal cells to attach to surfaces such as skin and mucosa and is considered a first step in the development of an infection [10]. In the biofilm, the fungus can hide from the immune system and also to some extent for various treatments aimed against the fungus. The results of the study showed that CHG was better than FLZ both at killing the fungal cells and preventing new biofilm from forming and dissolving already established "old" biofilm. This effect is absolutely crucial for successful treatment with antimycotics. These encouraging results form the basis of the planned study.

Hibitane® is an over-the-counter vaginal cream consisting of 1% chlorhexidine gluconate with the indication antiseptic use in vaginal examinations, especially during childbirth. The product has been used for a long time in various gynecological and obstetric surgical procedures. Hibitane® is approved during pregnancy and the cream is usually well tolerated [11]. There are only few studies that investigated how vaginal normal flora is affected by CHG. One human study showed a decrease in the number of lactobacilli a week after the vaginal application of 0.5% CHG every night for a week. After 30 days, the vaginal normal flora was basically fully recovered and the side effects were few [12]. In an animal study, no major effect was seen on the vaginal flora after 2 vaginal applications of CGH 0.25% at 24 hours apart [13].

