***Statistical methods:***

Analysis for differences over time for treatment efficacy, AEs, symptom- and examination score, impact on vaginal lactobacilli and relapses will be analyzed for all randomized patients (i.e. intent-to-treat ITT). Additionally, we will also examine efficacy for the per-protocol (PP) population. Four time points will be used to study the efficacy (proportion of participants with negative cultures for *Candida albicans*) in each treatment arm (baseline, 1w post-treatment, follow-up 3 and 6 months). We will examine the difference in means, proportions and median values using 95% confidence intervals (CI). The CI interval will be computed using 1) for a proportion in one sample and 2) logistic or multinomial logistic regression analysis.

Differences in baseline characteristics between the CHG and FLZ groups will be analyzed with Chi2 for categorical data, Mann Whitney U test for ordinal data, or t-test for continuous data to examine potential selection bias at randomization. Differences in drop-out rates across treatment arms will also be analyzed using Mann Whitney U test.

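### The group-by-time comparison of lactobacilli, read as an interaction that includes baseline, gives up power that a follow-up comparison adjusted for the Visit 2 grade would keep

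*Protocol*

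**What the plan says.** Protocol section 8.1.2 item 4 sets the readings: "The content of lactobacillus in vaginal wet mount will be analyzed and semi-quantified first at baseline/inclusion and then at 3 follow-ups". Table 1 confirms lactobacilli microscopy at Visits 2, 3, 4 and 5. Each reading is graded as normal or reduced. The same item then gives the comparison: "Differences in proportion of women with normal/reduced quantity between study groups x time will be analyzed".

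Section 10.2.1 places this endpoint among the analyses of differences over time, in the intention-to-treat set: "impact on vaginal lactobacilli and relapses will be analyzed for all randomized patients". The method offered there is general: "The CI interval will be computed using 1) for a proportion in one sample and 2) logistic or multinomial logistic regression analysis". No baseline covariate, random effect or clustering by woman is named, and none is ruled out. Section 10.3 adds a false-discovery-rate adjustment across the secondary outcomes.

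The Background section gives the reason for measuring lactobacilli: "One human study showed a decrease in the number of lactobacilli a week after the vaginal application" of 0.5% chlorhexidine, with near-complete recovery by 30 days. It also cites an animal study at 0.25% that saw no major effect. The Synopsis and the Background both make a small effect on lactobacilli one of the conditions for the hoped-for benefit of CHG.

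**The concern.** The natural reading of a comparison between groups by time, with baseline as the first time, is an interaction: the change from Visit 2 in one arm minus the change in the other. In a randomised trial both arms have the same expected Visit 2 prevalence. The interaction therefore estimates a baseline difference whose expectation is zero and subtracts it, which adds variance and removes no bias.

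Ordinary logistic regression on stacked visits adds a second loss. It treats a woman's readings as independent, so when they correlate positively the standard error of a within-woman contrast is too large.

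Both losses make a real difference harder to see. Here a missed difference would be read as CHG having little impact on lactobacilli, which is one of the findings the trial would use to support CHG. With 30 women per arm there is little power to spare.

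**Working it through.** **The plan's own figure.** None exists for this endpoint. The only sample-size figure, 23 per group for the primary outcome, reproduces with a one-sided 5% level: (1.645 + 1.282)² × 2 × 0.86 × 0.14 / 0.30² = 22.9, rounded up to 23. It does not bear on lactobacilli.

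**Inputs.** From the protocol: 30 per arm, 1:1 allocation, 5% level (taken as two-sided here) and a binary grade. Assumed, because the protocol gives none: prevalence of a reduced grade, effect size, and correlation between a woman's readings.

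**Hand calculation.** Assume 20% reduced in both arms at Visit 2, and at follow-up 20% on FLZ and 50% on CHG. The log odds ratio at follow-up is ln(0.5/0.5) − ln(0.2/0.8) = 1.386. The variance of one estimated logit is 1/(n p(1−p)): 1/(30 × 0.16) = 0.2083 at 20%, and 1/(30 × 0.25) = 0.1333 at 50%. Power is approximately Φ(z − 1.96).

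- Follow-up comparison, unadjusted: variance 0.2083 + 0.1333 = 0.3417, SE 0.585, z = 2.37, power about 66%.
- Interaction, visits treated as independent: two baseline terms are added, so 0.3417 + 2 × 0.2083 = 0.7583, SE 0.871, z = 1.59, power about 36%.
- Interaction, pairing modelled: take a correlation of 0.30 between the binary grades, which is roughly what a latent correlation of 0.5 gives. The covariances are 0.30 × 0.2083 = 0.0625 (FLZ) and 0.30 × √(0.2083 × 0.1333) = 0.0500 (CHG). The variance is 0.7583 − 2 × 0.1125 = 0.5333, SE 0.730, z = 1.90, power about 48%.

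The effect being estimated is the same 1.386 throughout. Only the variance changes.

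**Simulation.** 30 per arm, one follow-up visit, grades cut from correlated normal variables, reduced grade 20% v 48% or 40% v 71% (FLZ v CHG), Visit 2 prevalence equal to the FLZ value, no false-discovery adjustment.

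| Analysis | Power at latent correlation 0.5 (20% v 48% / 40% v 71%) | Range over 0.3-0.7 |
|---|---|---|
| Interaction, pairing ignored | 29% / 37% | 28-39% |
| Interaction, pairing modelled | 42% / 53% | 39-64% |
| Follow-up only, unadjusted | 62% / 68% | 62-69% |
| Follow-up, adjusted for Visit 2 grade | 66% / 72% | 66-77% |

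Dropping the interaction accounts for most of the gain. The adjustment itself adds about 0 to 9 points.

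**Type I error.** With pairing ignored and equal prevalences, the true standard deviation is √(1 − 0.30) = 0.837 of the one used. The real two-sided level is then 2 × [1 − Φ(1.96/0.837)], about 1.9%. Over the simulated scenarios it runs from about 0.5% to 3%.

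**Sensitivity.** Share of the adjusted analysis's power that the interaction keeps, over baseline prevalences of 20-50%:

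| Difference | Pairing modelled, latent correlation 0 / 0.5 / 0.9 | Pairing ignored, correlation 0-0.9 |
|---|---|---|
| 30 points | 46-57% / 57-73% / 70-91% | 26-57% |
| 40 points | 53-67% / 67-85% / 83-98% | 50-70% |

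The loss shrinks with a larger effect. It shrinks with higher correlation only when the pairing is modelled. With all four visits and a three-degree-of-freedom group-by-time test that uses the correlation, power for 30-point effects was 27-34% at correlation 0, 36-51% at 0.5 and 44-69% at 0.8.

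**The case against.** The strongest reply is that the protocol does not fix the model. The phrase in 8.1.2 item 4 names no interaction term and no reference visit, and could mean comparing the arms at each visit. The list of times in 10.2.1 that includes baseline, "in each treatment arm (baseline, 1w post-treatment, follow-up 3 and 6 months"), is written for culture efficacy. Covariates and clustering are commonly left to a statistical analysis plan, and one is listed as an attachment. On the per-visit reading the loss is only the few points that adjustment would add. This stands as a limit: a reader might infer that the plan rejects baseline adjustment, but it only fails to name it. It does not dispose of the point. A group-by-time comparison with baseline as the first reading is stated, and the interaction is its most natural meaning.

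Four stronger readings are tempting and are not supported.

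- That power is roughly halved. This needs a moderate effect together with pairing ignored or a weak correlation, and every input is assumed.
- That lactobacilli is a safety endpoint. Section 8.2 names two, adverse events and epithelial toxicity, and this is not one of them.
- That the effect of CHG on lactobacilli is known. The protocol cites one human study, at half this trial's concentration, and an animal study without a major effect.
- That Visit 3 should be the main time point because flora recovered within 30 days. That recovery followed a single week of use, whereas here weekly CHG continues up to Visit 4.

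**Conclusion.** The point holds as a correctable inefficiency in a stated secondary analysis. If the comparison is a group-by-time interaction including baseline, it has less power than a follow-up comparison adjusted for the Visit 2 grade. For a difference of about 30 points and latent correlation 0.3 to 0.7, power is about 28-39% (pairing ignored) or 39-64% (pairing modelled), against 66-77%. With pairing ignored the test is also conservative, at about 0.5-3% instead of 5%.

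These figures rest on assumed prevalences, effect and correlation, on a single follow-up visit, and on no false-discovery adjustment, so they show the relative loss and not the power of the planned test. With larger effects, or with high correlation properly modelled, the loss becomes small. The primary conclusion of the trial is not affected. The change is worth making because the error is towards missing an effect of CHG, and the better analysis uses data already in hand.

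**What to change.** In sections 8.1.2 item 4 and 10.2.1, replace the group-by-time wording for lactobacilli with the following. At each of Visits 3, 4 and 5, compare the arms by logistic regression of reduced versus normal grade on arm, with the Visit 2 grade as covariate, and report a risk difference with a 95% confidence interval. If the visits are modelled together, include only the three follow-up visits as outcomes, cluster by woman (for example by GEE), and keep the Visit 2 grade as covariate.

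The cost is a change of wording in the protocol, carried into the statistical analysis plan. No visit, sample or participant is added, since the Visit 2 grade is already collected. A rule is needed for any woman without a Visit 2 grade, for example a missing-category indicator.
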